## Abstract

**Background:**

Neonatal respiratory distress syndrome (NRDS) is a life-threatening condition marked by progressive respiratory failure due to pulmonary surfactant (PS) deficiency, typically presenting within hours of birth. Exogenous pulmonary surfactant replacement therapy has significantly reduced mortality associated with NRDS and improved clinical outcomes. The current standard of care involves the intubation-surfactant-extubation (INSURE) technique. However, emerging evidence suggests that the laryngeal mask airway (LMA) may serve as a viable noninvasive alternative for neonatal resuscitation and therapeutic administration. This randomized controlled equivalence trial aims to compare the clinical efficacy and safety profiles of LMA and INSURE in delivering PS for NRDS management.

**Methods:**

Some of the preterm infants diagnosed with NRDS and requiring the first treatment with PS were included in this study. The included subjects were randomly assigned to the LMA group (experimental group) and the INSURE group (control group) by means of envelopes, and were given PS treatment by LMA or INSURE, respectively, and the SF index (SpO_2_/FiO_2_) before and after the use of PS; the placement time of artificial airway, the episodes of hypoxemia, bradycardia and tachycardia during artificial airway placement; the amount of PS residue in the stomach after the use of PS; the incidence of the second use of PS, and the incidence of pneumothorax were also monitored in order to compare the effect and prognosis of the two methods of treating NRDS.

**Discussion:**

The use of PS with INSURE is currently the most prominent and classic method. Although some recent studies suggest that non-invasive use of PS through a laryngeal mask is also effective, relevant research remains limited. Through this trial, we aim to gather more data regarding the use of PS with a laryngeal mask and further validate its effectiveness.

**Trial registration:**

Name of the registry: A randomized controlled trial of pulmonary surfactant administration via laryngeal mask airway versus endotracheal intubation.

Trial identifying number: ChiCTR2500096315.

Date of registration in primary registry: 2025-01-21 00:00:00.

PID: 254631.

Country of recruitment: China.

URL of trial registry record: https://www.chictr.org.cn/showproj.html?proj=254631.

## Introduction

### Background {6a} {6b}

Pulmonary surfactant (PS) therapy, a groundbreaking advancement in neonatology, was pioneered by Fujiwara et al. in 1980 [1]. Over the past four decades, extensive clinical research has consistently validated the therapeutic efficacy of PS administration, demonstrating its remarkable ability to reduce neonatal mortality rates and enhance clinical outcomes in infants with respiratory distress syndrome (RDS) [2, 3]. In contemporary clinical practice, the intubation-surfactant-extubation (INSURE) technique remains the gold standard for PS administration. However, the field is currently undergoing significant evolution, with emerging noninvasive administration methods gaining increasing attention. These innovative approaches, including thin catheter delivery, laryngeal mask airway (LMA) application, and nebulization techniques, are either being actively implemented in clinical settings or undergoing rigorous investigation to optimize therapeutic delivery while minimizing invasive procedures [4–6].

The LMA has emerged as a promising noninvasive alternative for PS administration, with multiple clinical studies demonstrating its feasibility and therapeutic benefits. Research findings consistently indicate that LMA-assisted PS delivery significantly reduces supplemental oxygen requirements and decreases the need for mechanical ventilation in infants, offering a less invasive option compared to traditional methods [7–9]. These positive outcomes highlight the potential of LMA as a viable approach in neonatal respiratory care. However, despite these encouraging results, the current body of evidence remains limited, particularly in direct comparative studies evaluating the efficacy of LMA against the well-established INSURE procedure. This knowledge gap underscores the need for further rigorous research to establish the optimal application of LMA in PS administration protocols.

### Objectives {7}

In this study, we aimed to evaluate compare with INSURE, whether the administration of surfactant via LMA can be used as an effective alternative for the treatment of NRDS in preterm infants.

### Trial design {8}

This trial is a single-center randomized controlled trial. The included samples will be randomized into the experimental group (LMA group) and the control group (INSURE group) by methods of envelopes. The study is an equivalence trial designed to demonstrate that LMA and INSURE are equally effective in the treatment of NRDS using PS.

## Methods: participants, interventions, and outcomes

### Study setting {9}

This study will be conducted in the neonatal unit of West China Second Hospital, a teaching hospital in Chengdu, China.

### Eligibility criteria {10}

The inclusion and exclusion criteria of this study were primarily developed with reference to existing clinical studies on the use of LMA in infants with NRDS [7, 8, 10–15]. The specific criteria are as follows:

#### Inclusion criteria

Gestational age between 30 0/7 and 36 6/7 weeks, and/or birth weight ≥ 1500 g.Age within 48 hours after birth.Use of a noninvasive ventilator for more than 30 minutes.Nasal continuous positive airway pressure (nCPAP), bi-level positive airway pressure (BiPAP), or non-invasive positive pressure ventilation (NIPPV) support ≥ 6 cmH_2_O, or high-flow nasal cannula (HFNC) support ≥ 6 L/min.Need for fraction of inspired oxygen (FiO_2_) ≥ 0.30 to maintain pulse oximetry oxygen saturation (SpO_2_) levels between 90 and 94%.Radiological evidence of RDS.

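### As written, the and/or between gestational age and birth weight admits term infants of 1500 g or more who meet the other criteria, although the trial's question concerns preterm infants

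*Protocol article*

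**What the plan says.** The first item under Inclusion criteria is "Gestational age between 30 0/7 and 36 6/7 weeks, and/or birth weight" of at least 1500 g. The remaining items set limits on postnatal age ("Age within 48 hours after birth"), on the duration and level of noninvasive support, on oxygen requirement ("Need for fraction of inspired oxygen (FiO_2_) ≥ 0.30") and on radiological signs of RDS. None of them mentions prematurity. The Exclusion criteria cover earlier ventilation or surfactant, anomalies, pneumothorax, need for invasive ventilation, outside transfers and continued intubation. None concerns gestational age or term birth.

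The stated population is narrower. The Objectives ask whether surfactant through the laryngeal mask "can be used as an effective alternative for the treatment of NRDS in preterm infants", and the abstract's Methods paragraph opens with "Some of the preterm infants diagnosed with NRDS".

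On analysis, section {20c} bases the primary result on every randomised infant and adds a per-protocol analysis that removes infants who did not complete or had major protocol violations. Section {20b} states that there are no subgroup analyses.

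**The concern.** *And/or* is an inclusive or. At 1500 g and above the gestational-age window excludes nobody, and inside the window the weight floor excludes nobody. The group that conflicts with the trial's question is infants of 37 weeks or more who qualify on weight.

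Two things are at stake. First, the enrolled population may differ from the one named in the objective, and no planned analysis would recover it. Second, the test is an equivalence test on 60 infants, so a modest number from another population could shift the observed difference or the spread. The wording also lets two screeners apply the same line differently, one as *and*, the other as *or*.

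**Working it through.** **Step 1: what the criterion admits.** All rows assume that the other inclusion and exclusion criteria are met.

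| Gestational age | Weight | Eligible if *and* | Eligible if *or* | Preterm |
|---|---|---|---|---|
| 30 0/7–36 6/7 | ≥ 1500 g | yes | yes | yes |
| 30 0/7–36 6/7 | < 1500 g | no | yes | yes |
| under 30 weeks | ≥ 1500 g | no | yes | yes, but outside the window |
| 37 weeks or more | ≥ 1500 g | no | yes | **no** |

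Only the last row contradicts the Objectives and the abstract. Rows two and three show that neither limit is firm, but those infants are preterm.

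**Step 2: whether the analysis plan corrects it.** Intention-to-treat keeps all four rows. An infant who meets the criterion as printed is not a protocol violation, so the per-protocol set keeps all four as well. Regression adjustment, planned only if baseline imbalance is found, does not change who is analysed. No subgroup analysis is planned.

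**Step 3: the plan's own sample size.** Inputs from Sample size {14}: margin 0.45, SD 0.41, true difference 0, power 90%. The pooled SD is √((0.5² + 0.3²)/2) = 0.412, as stated. The normal approximation for two one-sided tests is n = 2 × [SD × (z(1−α) + z(0.95)) / margin]².

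- α = 0.025 per side: 2 × (0.41 × 3.6048 / 0.45)² = 2 × 3.2844² = 21.57, so 22. The exact t-based calculation gives 23 (power 90.7%). This reproduces the plan.
- α = 0.05 per side, which is what the 90% CI rule in section {20a} implies: 17.97, so 18; exact 19. At 23 per arm the power is 95.7%.
- Dropout: 23 / 0.80 = 28.75, so 29, as stated.

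The eligibility wording changes none of these figures. The next steps use the 90% CI rule at 23 per arm.

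**Step 4: scenario A, attenuation.** Assumptions that are not in the documents: a share q of each arm lies outside the window with no arm difference, the true difference in the preterm infants is exactly 0.45, and the SD stays at 0.41. The mixed difference is μ = (1 − q) × 0.45. Equivalence is declared when the observed difference lies within ±h, with h = 0.45 − t(0.95; 44) × s × √(2/23). The probability of this is integrated over the chi-square distribution of s².

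| q | μ | Declares equivalence, 23 per arm | 30 per arm |
|---|---|---|---|
| 0 | 0.450 | 5.0% | 5.0% |
| 10% | 0.405 | 10.1% | 11.0% |
| 20% | 0.360 | 18.1% | 21.1% |

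**Step 5: scenario B, added spread.** Assumptions that are not in the documents: no true arm difference anywhere, but infants outside the window have a mean SF index shifted by m. Then SD = √(0.41² + q(1 − q)m²).

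| m | q | SD | Power, 23 per arm |
|---|---|---|---|
| – | 0 | 0.410 | 95.7% |
| 0.5 | 10% | √(0.1681 + 0.0225) = 0.437 | 92.8% |
| 0.5 | 20% | √(0.1681 + 0.0400) = 0.456 | 90.1% |
| 1.0 | 10% | 0.508 | 81.1% |
| 1.0 | 20% | 0.573 | 67.2% |

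Scenario A makes a claim of equivalence easier and scenario B makes it harder.

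**The case against.** **The criterion should be read with the rest of the protocol.** The Objectives and the abstract name preterm infants, so *and/or* might be meant only to let in preterm infants who miss one of the two limits. Nothing shows that term infants are intended or have been enrolled. This is a fair reading of intent, but screeners apply the eligibility list, and that list contains no requirement of prematurity. The contradiction stands.

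**Not every infant of 1500 g or more is eligible.** The limits on age, support level, oxygen need and radiology, together with the exclusions, still apply and are likely to keep the number of term infants small. This stands and limits the size of the problem.

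**Dilution is not established.** A reader might infer that the wording biases the trial towards equivalence. The documents do not support that. They give no share of infants outside the window and no SF index or treatment effect by gestational age. Scenario A needs three assumptions together, and the zero arm difference is doubtful because these infants also have radiological RDS and an oxygen need. Scenario B points the other way. This objection stands in full.

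**Scenario A is not an inflated type I error for the randomised population.** With a mixed difference of 0.405 or 0.36, the arms are within the margin for the infants actually enrolled. The 10% and 18% describe the risk of carrying that conclusion over to preterm infants whose own difference is at the margin. This also stands.

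**A late amendment may reach few infants.** Recruitment began in October 2023 and is estimated to end in June 2026, and an amendment needs ethics approval. This is true, which is why the restricted analysis matters as well as the rewording.

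**Conclusion.** The point holds as a contradiction between the eligibility rule and the stated population, and that part needs no numerical assumption. As printed, a term infant of 1500 g or more who meets the other criteria is eligible, and no planned analysis would separate such infants from the preterm ones.

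The consequence for the equivalence test is a conditional risk of unknown size and direction. With 10–20% of infants outside the window (6 to 12 of 60, an assumed range), the chance of declaring equivalence when the preterm difference is 0.45 is about 10–18% instead of 5% under scenario A. Power falls from about 96% to 93–90% under scenario B with a mean shift of 0.5. The documents do not say which applies, or whether any such infant will be enrolled. The sample size of 23 per group is unaffected.

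**What to change.** Reconcile the first inclusion criterion with the Objectives and the abstract:

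1. Make preterm gestation a required criterion, using the stated window of 30 0/7 to 36 6/7 weeks if that is the range the sponsor intends.
2. Give birth weight a single operator: either a second required criterion or no criterion. The choice is the sponsor's.
3. Keep infants already enrolled on weight alone in the intention-to-treat analysis. Prespecify one sensitivity analysis of the primary outcome restricted to the preterm window, with the same margin and 90% CI rule, and report it beside the primary result with the number of infants it leaves out.

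The cost is a short amendment through the ethics committee, one extra analysis and possibly a few infants lost to recruitment. If no infant outside the window has been enrolled, the restricted analysis coincides with the primary one and the question is closed.

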#### Exclusion criteria

History of prior invasive mechanical ventilation.Previous PS therapy.Congenital anomalies.Pneumothorax.Requirement for direct invasive ventilation.Transfer from external hospitals.Need for continued endotracheal intubation after the INSURE procedure.

### Who will take informed consent? {26a}

Trained researchers will inform the patients about the details of the trial and explain any potential adverse outcomes. Informed consent forms have been obtained from the parents of all infants participating in the trial.

### Additional consent provisions for collection and use of participant data and biological specimens {26b}

Regarding the collection and use of participant data, these data will be collected through standardized procedures. If any follow-up studies or additional analyses related to this research are conducted in the future, the data will be retrieved and used for those studies. Furthermore, access to these data will be restricted to authorized personnel and will only be used for the purposes outlined in the informed consent form. As for biological specimens, this study does not involve the collection of biological samples, as all data are obtained through non-invasive clinical monitoring procedures, in line with the standards for observational research.

## Interventions

### Intervention description {11a}

Randomization will be performed immediately upon confirmation of eligibility. Following group allocation, infants will commence PS therapy according to their assigned intervention protocol.

#### Artificial airway

LMA size 1, 1.5 (classic);

Endotracheal tube without cuff.

#### Pulmonary surfactant (PS)

All patients will receive the same PS preparation.

#### Premedication

In the LMA group, all patients underwent a standardized pre-procedural protocol involving the application of lidocaine spray for effective surface anesthesia. This preparatory step was implemented to ensure patient comfort and optimize the conditions for successful LMA placement and subsequent pulmonary surfactant administration. The use of topical lidocaine, a well-established local anesthetic agent, served to minimize potential discomfort and airway reflexes during the procedure, thereby enhancing the overall safety and tolerability of this noninvasive approach.

### Operating procedure

#### Experimental group: LMA group

Suction secretions and position the patient correctly.Administer lidocaine spray for topical anesthesia.Insert the LMA.Confirm the correct position of the LMA by observing chest movement, auscultating the lungs, and monitoring SpO_2_ for 1 minute.Administer PS through the LMA.Use a T-piece to provide high-frequency, low tidal volume positive pressure ventilation concurrently.During the procedure, confirm the uniform distribution of PS by auscultation.Periodically aspirate the cuff to confirm the LMA seal.After the PS administration, continue positive pressure ventilation until no significant wet crackles are heard upon auscultation.Remove the LMA and continue noninvasive ventilation.

#### Control group: INSURE group

Suction secretions and position the patient correctly.Perform endotracheal intubation, then connect to the T-piece for positive pressure ventilation.Confirm the correct position of the tube by auscultation, observing chest movement, checking for condensation on the tube, and monitoring SpO_2_ for 1 minute.Administer PS through the endotracheal tube.Continuously use the bag-valve-mask for high-frequency, low tidal volume positive pressure ventilation.During the procedure, confirm the uniform distribution of PS by auscultation.After PS administration, continue positive pressure ventilation with the T-piece until no significant wet crackles are heard upon auscultation.Remove the endotracheal tube and continue noninvasive ventilator support.

### Criteria for discontinuing or modifying allocated interventions {11b}

Intervention will be terminated if, during or after the procedure, the infant experiences unrelieved worsening of respiratory distress, severe hypoxia, or a significant increase in ventilator settings requiring endotracheal intubation or prolonged intubation. If the guardian of an enrolled infant requests to withdraw from the study, their decision will be fully respected.

### Strategies to improve adherence to interventions {11c}

Before the study begins, the research team will undergo protocol-based training to ensure a clear understanding of their respective roles and responsibilities. Pediatricians will assess whether the infant meets the criteria for PS administration, respiratory therapists will be responsible for the intervention and data recording, and nurses will assist with the intervention. Data recorders will also receive training to ensure consistency in data collection. Any challenges encountered during the trial will be promptly addressed.

### Relevant concomitant care permitted or prohibited during the trial {11d}

All enrolled infants will receive standardized clinical care in accordance with the established neonatal intensive care protocols throughout the study period, with all necessary therapeutic interventions fully maintained. During the intervention, standard supportive procedures will be followed as required.

### Ancillary and post-trial care {30}

Participants will receive necessary post-trial care based on their clinical needs, including follow-up for any trial-related adverse effects. Compensation for harm caused by trial participation will be provided according to ethical guidelines and local regulations, covering medical expenses and related costs. Participants will be informed of these provisions before enrollment, and ongoing medical support will be arranged if needed.

### Outcomes {12}

#### Primary outcome measures

The SF index (SpO_2_/FiO_2_) at 1 day after PS administration.

### Secondary outcome measures

The SF index before and after the administration of PS.The main monitoring time points are: before PS use and at 1 minute, 3 hours, 6 hours, and 12 hours after PS administration.Time taken for placement.Number of SpO_2_ fluctuations, episodes of bradycardia, and tachycardia during intubation.Whether PS could be aspirated from the stomach after administration.Administration of a second dose of PS due to NRDS (administered in the same manner as the first dose) (ethically assessed).Incidence of pneumothorax.

### Participant timeline {13}

**Table Tabb:**
[figure not shown]

### Sample size {14}

The sample size for this equivalence trial was determined a priori based on the primary outcome—the SF index at 1 day after PS administration. The calculation was performed using EmpowerStats (www.empowerstats.com) and R software (version 4.1.0, R Foundation for Statistical Computing, Vienna, Austria). Based on pre-experimental data, the mean SF index was 4.5 in both the LMA and INSURE groups, with standard deviations of 0.5 and 0.3, respectively, yielding a pooled SD of approximately 0.41. For this equivalence design, the sample size was determined according to a predefined equivalence margin (Δ) of 0.45, which was considered clinically acceptable by expert consensus as it represents less than a 10% difference from the baseline mean value.

Using these parameters (*Δ* = 0.45, SD = 0.41, *α* = 0.05, power = 90%), a two one-sided test (TOST) procedure indicated that a minimum of 23 participants per group was required. Allowing for an anticipated 20% dropout rate, we planned to enroll 29 participants per group, for a total of 58 infants. To facilitate recruitment, the final target sample size was rounded to 60 infants (30 per group).

This methodological approach underscores our commitment to rigorous scientific standards and enhances the reliability and validity of our trial outcomes.

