## Statistical methods

### Statistical analysis {20a}

All analyses will be performed using SPSS software (IBM Corp., Armonk, NY, USA). Continuous variables will be summarized as means ± SD or medians (IQR), and categorical variables as *n* (%). The primary outcome, the SF index at 1 day after PS administration, will be evaluated for clinical equivalence between the LMA and INSURE groups using the TOST procedure based on an independent-samples t-test. Equivalence will be concluded if the entire 90% CI of the mean difference lies within the predefined margin of − 0.45 to + 0.45; if normality is not met, a nonparametric test will be applied. Secondary outcomes will be analyzed using t-tests or Mann–Whitney U tests for continuous variables and logistic regression or Fisher’s exact test for binary variables, as appropriate. If baseline imbalances are identified, multivariable linear or logistic regression will be performed to obtain adjusted estimates. A two-sided *P*-value < 0.05 will be considered statistically significant.

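### The stated minimum of 23 per group is not the 90%-power figure for the planned equivalence test: under the 90% CI rule the minimum is 19, and 23 gives about 96% power

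*Protocol article*

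**What the plan says.** Under Sample size {14}, the protocol article takes a "predefined equivalence margin (Δ) of 0.45" and pilot data "with standard deviations of 0.5 and 0.3, respectively, yielding a pooled SD of approximately 0.41"; the pilot mean was 4.5 in each arm, LMA and INSURE alike. With alpha 0.05 and 90% power it concludes that "a two one-sided test (TOST) procedure indicated that a minimum of 23 participants per group was required". A 20% dropout allowance raises this to 29 per group, and rounding gives 30 per group, 60 in all. The section does not say whether alpha 0.05 applies to each one-sided test or is two-sided.

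Under Statistical analysis {20a}, the primary outcome is analysed "using the TOST procedure based on an independent-samples t-test", with this rule: "Equivalence will be concluded if the entire 90% CI of the mean difference lies within the predefined margin", the limits being −0.45 and +0.45. The paragraph ends with a general statement: "A two-sided *P*-value < 0.05 will be considered statistically significant".

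**The concern.** A sample size section should let a reader go from the inputs to the number. Here every input is given, yet the number does not follow from them under the test that the analysis section specifies. A 90% interval means 5% in each tail, and at that level 23 is larger than 90% power requires. Either the power or the minimum is misreported, or the calculation used a different per-side alpha from the analysis.

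The last possibility is why this needs settling. In an equivalence trial the per-side alpha is the risk of declaring equivalence when the true difference sits at the margin. The sample size section leaves that level unstated, so the reader has to infer it from the width of the interval in another section.

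**Working it through.** **Inputs, all from the protocol article.** Margin Δ = 0.45; SD = 0.41; true difference 0 (equal pilot means); alpha 0.05; power 90%; 1:1 allocation; t-based TOST judged by a 90% CI, so 5% per side.

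**SD.** √((0.5² + 0.3²)/2) = √0.17 = 0.4123, given as 0.41. This is correct.

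**Normal approximation, 5% per side, 90% power.** With a true difference of zero, the type II error is shared between the two tests:

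n = 2 × [SD × (z(1−α) + z(1−β/2)) / Δ]²
= 2 × [0.41 × (1.645 + 1.645) / 0.45]²
= 2 × 2.997² = 17.97, so 18 per group.

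**Exact t-based power.** For each n, SE = 0.41 × √(2/n) and df = 2n − 2. Power is the probability that |difference| + t(1−α, df) × estimated SE is below 0.45, integrated over the distribution of the sample variance.

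| n per group | 5% per side (90% CI) | 2.5% per side (95% CI) |
|---|---|---|
| 18 | 88.6% | 78.4% |
| 19 | **90.6%** | 81.7% |
| 22 | 94.7% | 89.0% |
| 23 | **95.7%** | 90.7% |
| 24 | 96.4% | 92.2% |
| 30 | 98.9% | 97.4% |

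Under the planned rule the first n to reach 90% is 19.

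**Can rounding or the unequal SDs explain 23?** No. The unrounded SD of 0.4123 also gives 19. Simulation with SDs of 0.5 and 0.3 gives 90.1% power at 19 and 95.3% at 23, at 5% per side. Using z(power) in place of z(1−β/2) gives 15 at 5% per side and 18 at 2.5%.

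**What does reproduce 23?**

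- 2.5% per side with 90% power: 2 × [0.41 × (1.960 + 1.645)/0.45]² = 21.57; exact 23.
- 5% per side with 95% power: 2 × [0.41 × (1.645 + 1.960)/0.45]² = 21.57; exact 23. The two z-values have simply changed places.
- A 20% buffer on 19: 19 × 1.2 = 22.8, rounded up to 23.

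The figure alone cannot tell these apart.

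**Dropout step.** 23/0.8 = 28.75, so 29, which is correct. From 19 the same step gives 19/0.8 = 23.75, so 24 per group, 48 in all. With 30 enrolled and 20% lost, 30 × 0.8 = 24 per arm are evaluable.

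**The case against.** The best defence is that nothing is at risk. Under the usual TOST convention, alpha 0.05 means 5% per test, which is exactly what a 90% CI delivers, so the two sections agree on alpha. On that reading the trial is larger than its stated inputs require, and its power exceeds 90%. This stands, and it limits the point to a misreported figure. It does not rescue the claim that 23 is the minimum at 90% power.

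Three stronger readings are tempting, and the documents do not support them.

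- **That the trial was sized at 2.5% per side and is now judged at a laxer 5%.** A reader might infer this because 23 is the exact answer for a 95% CI. No section states 2.5% per side or a 95% CI, and 23 fits 95% power at 5% per side equally well. A doubled risk of false equivalence is therefore not shown.
- **That a ceiling on the SF index makes this in effect a one-sided claim.** A value of 4.5 + 0.45 = 4.95 is above the 1.00/0.21 = 4.76 attainable in room air. But the margin applies to the difference in means. It is out of reach only if the INSURE mean really is near the pilot 4.5; with a mean of 4.2, a difference of +0.45 gives 4.65, which is attainable. The argument also has no bearing on 19 against 23.
- **That the general two-sided P-value rule overrides the primary test.** The primary outcome has its own explicit interval rule, and the general sentence comes after the secondary and adjusted analyses. A clarifying phrase would help, but there is no conflict of substance.

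**Conclusion.** The point holds as a reporting error in the sample size justification. For the inputs given and the 90% CI rule, the minimum is 19 per group; the stated 23 is 4 per group higher and corresponds to about 96% power, not 90%. The result assumes a true difference of zero and an SD of 0.41, both taken from the article, and it survives the unrounded SD and the unequal pilot SDs.

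The direction is conservative. At the planned enrolment, power stays above 90% whether the interval is 90% or 95%. The type I error of the planned rule matches the stated alpha, and the primary conclusion is not endangered. This is a minor correction, not a must-fix.

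**What to change.** In Sample size {14}, state that alpha is 5% for each one-sided test, matching the 90% CI, and make one of two changes:

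1. Keep 23 per group and restate the power as about 96%. This leaves the steps to 29, 30 and 60 intact and is the smaller edit.
2. Restate the minimum as 19 per group (24 after dropout), and say that 60 infants are kept as a deliberate excess, with about 96% power at 24 evaluable per arm.

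In Statistical analysis {20a}, add that the two-sided 0.05 rule does not govern the primary equivalence test.

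The cost is two or three sentences. Neither the number of infants nor the decision rule changes.

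Only if the sponsor's records show that 2.5% per side was intended should the analysis section move to a 95% CI. Power would then be 90.7% at 23 and 92.2% at 24 per group. That changes the primary decision rule, so it needs a formal amendment with ethics approval, as Protocol amendments {25} requires, made before the data are analysed. Trial status gives an estimated recruitment completion of June 2026.
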